### Quality monitoring

The trial will be conducted according to the Standard Operating Procedures (SOPs) of the OCTRU. There will be standardised initial training to all CORKA trial assessors and clinical staff involved in delivering the interventions at all sites. After the training the following procedures will be used to promote consistency and high-quality trial procedures across all sites:A member of the CORKA team will observe each assessor perform at least one of their assessments to ensure that they take place as per protocol. Repeat visits will be undertaken should any concerns arise until reliable and valid assessments occurWithin 2 weeks copies of all assessment forms will be sent to the trial office for review in order to identify any issues concerning missing data or poorly completed forms. Any issues or concerns will be discussed with individual assessorsA member of the CORKA team will check each site’s trial master file and meet with researchers and clinicians from each site on an annual basis (or more frequently should this be necessary)

### Intervention compliance

Compliance with the test intervention will be defined as fulfilling at least four treatment sessions. The number of physiotherapy visits and the content of the treatment sessions will be recorded using clinician-completed treatment logs and patient exercise and participation diaries. A member of the CORKA team will observe clinical staff perform one of their treatments to ensure that all treatments adhere to the protocol. Clinical staff will be asked to complete a treatment log for each attendance, providing an approximate estimation of the time spent on key intervention components and detailing and explaining any deviations from the protocol. Clinician compliance to the treatment protocol will be assessed and monitored by analysis of the treatment logs and site monitoring visits.

### Retention of participants

The study has two follow-up time points, at 6 and 12 months post randomisation. Follow-up can take place at the participant’s own home or at the hospital, depending on where the baseline took place, i.e. the location is consistent at participant level. Local site staff will organise the follow-up and liaise directly with the participant to organise the follow-up visits. Once confirmed, an appointment reminder letter or email can be sent out to the participants with the appropriate questionnaire.

An intention-to-treat analysis will be carried out; therefore, all participants remain in the study irrespective of whether they receive or continue with their allocated treatment (unless the participants themselves withdraw consent).

### Health economics

Health economics analysis will compare the cost-effectiveness over 1 year of providing the community-based intervention against standard care. The economic evaluation will take the form of a cost-utility analysis from a societal perspective and quality-adjusted life years (QALYs) will be used as the main health outcome measure. A micro-costing approach will be used to calculate costs of the home-based rehabilitation intervention and data will be collected from each trial participant on NHS and social care contacts up to 12 months through the use of a Participant Diary. Assessments of the health-related quality of life (HRQoL) of participants in each arm of the trial will be conducted using the EQ-5D-5L instrument at baseline, 6 and 12 months. Utility values derived from the EQ-5D-5L data will be combined with patient survival data and used to estimate QALYs for each patient up to 12 months.

Mean (standard deviation) costs and QALYs per patient will be estimated for each arm of the trial. The difference (95 % confidence interval (CI)) in mean costs and QALYs between trial arms will be estimated and, if necessary, an incremental cost-effectiveness ratio (ICER) calculated to determine the additional cost of generating one additional QALY. Results will be presented from an NHS, patient and societal (including informal care) perspective as recommended by current guidance. Cost-effectiveness acceptability curves will be used to determine the probability that the home rehabilitation programme is cost-effective at different values of society’s willingness to pay per QALY.

### Qualitative study

The nested qualitative study will provide a picture of the issues facing people with an expected poorer outcome after KA – particularly around expectations of outcome rehabilitation and outcomes on the level of function, activity and participation.

The qualitative study will take place in selected sites for a small number of participants (approximately 15 participants, in addition to approximately 15 members of staff). This number of participants is consistent with qualitative methodology. There will be a separate consent process before the interviews are carried out. Recruitment will take place throughout the study to ensure a spread of participants that is representative of the recruited population. Purposive sampling will be used to achieve a sample of participants which includes: female and male participants, those with differing levels of function and disability selected using their baseline LLFDI score and patients of varying activity levels. In addition, a sample of clinical staff who have delivered the intervention from differing professional backgrounds, physiotherapists, occupational therapists and rehabilitation assistants, will be interviewed.

Participants will be invited to take part in in-depth semistructured interviews following the intervention. Interviews will be held at a convenient time and location for each participant, from previous experience this is most likely to be at participant’s homes. The development of the interview schedule will be iterative and the questions asked may develop and change as the interviews are conducted. The interviews will be digitally recorded and fully transcribed. Field notes and memos will be recorded using a digital notepad. Audio recordings will be transcribed verbatim and coded. Interview data will be analysed using Smith’s experiential approach of Interpretative Phenomenological Analysis [41]. NVivo software will be used to assist in managing and presenting the findings. Participants will be offered the opportunity to view a summary of their results, providing an opportunity for them to contribute any additional comments. The research team will discuss the development of themes as the research progresses with the aim of providing different perspectives and enhancing the development of the themes.

### Data and statistical analysis

#### Sample size

Since the LLFDI has not been used widely there is currently little information from the existing literature about the value for the minimal clinically important difference or about the likely treatment difference in LLFDI component scores for this type of study. Therefore, our sample size calculation is based on a moderately small standardised effect size of 0.275, which is a value that we expect to be clinically important and associated with small but worthwhile benefits in rehabilitation trials. Six hundred and twenty participants (310 per arm) are required to detect a standardised effect size of 0.275 with 90 % power, 5 % (two-sided) significance and allowing 10 % loss to follow-up. This standardised effect size is equivalent to detecting around a 3-point difference on the LLFDI between treatment arms assuming a standard deviation of 10.91. The DMSC will be reviewing this assumption and monitoring the standard deviation.

Fifteen participants were randomised during an internal pilot study and will be used in the final analysis.

### Statistical analysis

The study will be reported according to the Consolidated Standards of Reporting Trials (CONSORT) 2010 Statement utilising the nonpharmacological treatment interventions and patient-reported outcome extensions [42, 43].

The principal comparisons will be performed on an intention-to-treat basis. The results from the trial will be presented as comparative summary statistics (i.e. difference in means) with 95 % CIs. The primary outcome will be analysed using a linear mixed effects method with repeated measures, on outcome measurements at 6 and 12 months, adjusting for baseline score and stratification/variables. An interaction between time and randomised group will be fitted to allow estimation of treatment effect at each time point. We will formally assess the distribution of the change from baseline for evidence of departure from normality. If necessary, data will either be transformed or analysed using a nonparametric equivalent. Similar approaches will be carried out for other continuous outcomes.

The nature and mechanism for the missing outcomes will be investigated, though mixed effects models that implicitly account for data following a missing-at-random mechanism. Sensitivity analyses will be carried out to examine the robustness of the results with different assumptions being made about departures from randomisation policies and handling of missing data.

A Statistical Analysis Plan (SAP) containing a more detailed account of the proposed statistical analysis will be drafted early in the trial and approved by the Independent Monitoring Committee for the trial prior to the primary analysis data lock and prior to the randomisation data being added to the database. The data analysis plan will consider in detail the need for baseline covariate adjustment. Any changes at this time will be incorporated into the final SAP and signed off as per current OCTRU Standard Operating Procedures (SOPs). Any changes/deviations from the original SAP will be described and justified in the protocol and/or in the final report, as appropriate.

The trial will be deemed a success based on the primary outcome of the total LLFDI based on the *p* value and if the lower bound of the 95 % CI is greater than 3 points.

Complier-average causal effect (CACE) will be estimated to assess the impact of the intervention compliance on the effect of the interventions.

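### A normality check on change from baseline, rather than on model residuals, can move the primary analysis off the LLFDI-point scale that the success rule needs

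*Protocol article*

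**What the plan says.** All the relevant text is in the Statistical analysis section of the protocol article.

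- Primary model: "The primary outcome will be analysed using a linear mixed effects method with repeated measures, on outcome measurements at 6 and 12 months", adjusted for the baseline score and the stratification variables.
- Effect at each visit: "An interaction between time and randomised group will be fitted to allow estimation of treatment effect at each time point".
- Distributional check: "We will formally assess the distribution of the change from baseline for evidence of departure from normality".
- Consequence of the check: "If necessary, data will either be transformed or analysed using a nonparametric equivalent".
- Scope: "Similar approaches will be carried out for other continuous outcomes". This follows the two sentences above, so the check and its fallback cover the primary outcome and are then extended to the other continuous outcomes.
- Effect measure to be reported: "comparative summary statistics (i.e. difference in means) with 95 % CIs".
- Success on total LLFDI is judged "based on the *p* value and if the lower bound of the 95 % CI is greater than 3 points".

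The section defers further detail to a SAP, to be approved before data lock and before the allocation data are added to the database. That SAP is not shown.

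**The concern.** Two stated parts of the plan do not fit the rest of it.

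First, the check looks at the wrong quantity. A linear mixed model assumes approximate normality of the residuals and random effects, given baseline, arm, visit and site. The marginal change score is neither the modelled outcome nor a residual. Its shape partly reflects the shape of the baseline distribution, about which the model assumes nothing.

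Second, the remedy may leave the scale on which the trial is judged. The reported effect is a difference in means, and success is a confidence bound in LLFDI points. A transformed analysis gives a bound on another scale. A standard rank test gives no mean difference adjusted for baseline and site, and no estimate by visit. The protocol does not say how the 3-point rule would then be applied.

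At stake is whether the primary result can always be read against the stated criterion, and whether the choice of primary method is settled before the outcome data are seen.

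**Working it through.** **1. Inputs and the plan's own figure.** The Sample size section plans to "detect a standardised effect size of 0.275 with 90 % power, 5 % (two-sided) significance and allowing 10 % loss to follow-up", with 620 patients (310 per arm) and an SD of 10.91.

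- Per arm: 2 × (1.960 + 1.282)² / 0.275² = 278 after rounding up.
- With 10% loss: 278 / 0.90 = 309 per arm, 618 in total, against 620 stated. The figure reproduces.
- Effect in points: 0.275 × 10.91 = 3.00.
- Evaluable patients: 620 × 0.90 = 558, or 279 per arm.

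**2. What the success rule needs.** Without adjustment, at 279 per arm:

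- SE = 10.91 × √(2/279) = 0.92 points.
- 95% CI half-width = 1.96 × 0.924 = 1.81 points.
- Observed difference needed = 3 + 1.81 = 4.81 points.

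Baseline adjustment would shorten the interval. Either way, the rule compares a bound in raw LLFDI points with 3, so it needs an estimate on that scale.

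**3. Change compared with residuals.** Illustrative simulation: 4,000 runs per row, 279 per arm, one follow-up visit, a baseline-adjusted linear model, and Shapiro-Wilk at 5% as one possible form of the check. Assumptions not in the protocol: baseline-outcome correlation 0.5; skewed baseline drawn as exponential (skewness 2); skewed residuals drawn as gamma with shape 2 (skewness 2/√2 = 1.41).

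| Scenario | True difference (points) | Test rejects: change | Test rejects: residuals | Model rejects no effect | 95% CI coverage |
|---|---|---|---|---|---|
| All normal | 0 | 4.5% | 5.2% | 5.2% | 94.8% |
| All normal | 3 | 5.0% | 4.4% | 95.6% | 94.5% |
| Skewed baseline, normal residuals | 0 | 55.1% | 4.9% | 4.9% | 95.1% |
| Skewed baseline, normal residuals | 3 | 53.0% | 5.6% | 96.5% | 94.8% |
| Skewed residuals | 0 | 100% | 100% | 4.8% | 95.3% |
| Skewed residuals | 3 | 100% | 100% | 96.0% | 94.6% |

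In the skewed-baseline rows every model assumption holds, yet the check on change raises an alarm in more than half the runs. The reason can be seen directly. In SD units, change = (0.5 − 1) × baseline + √0.75 × residual. Its variance is 0.25 + 0.75 = 1 and its skewness is (−0.5)³ × 2 = −0.25, all of it inherited from the baseline.

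**4. Whether a switch would be needed.** In the skewed-residual rows normality is always rejected, and the untransformed model still has 4.8% type I error and about 95% coverage. A simpler simulation agrees (n = 558, 1,500 replicates). Shapiro-Wilk rejected in about 73% of trials at skewness 0.3, 93% at 0.4, 99% at 0.5 and 86% with t-distributed tails on 8 degrees of freedom. The two-sample t-test on the same kinds of data had type I error of 4.9–5.2%. These rejection rates describe one possible form of the check. They are not the probability that this trial would change its analysis.

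**5. The fallbacks set against the plan's commitments.**

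| Analysis | CI in LLFDI points | Planned adjusted mean difference by visit |
|---|---|---|
| Stated mixed model | Yes | Yes |
| Transformed outcome | No | No, the scale changes |
| Standard rank test | Not from the test itself | No |
| Hodges-Lehmann shift | Yes | No, a location shift |
| Bootstrap of the mixed model | Yes | Yes |

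The protocol names none of the last four.

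**The case against.** The strongest reply is that the text is a conditional permission. It names no test, no significance level and no automatic trigger, and a SAP approved before allocation data are added could fix all of these. The distribution could also be judged on pooled data, blind to arm, though the protocol does not promise this. That stands, and it limits the point in three ways.

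- A reader might infer that the primary analysis will be switched. The text does not say so, and rejection rates for an assumed Shapiro-Wilk rule cannot stand in for that probability.
- A reader might infer that the 3-point comparison would become impossible. That is too strong. A Hodges-Lehmann shift or a bootstrap gives an interval in points, and a bootstrap of the mixed model keeps the planned estimate. What holds is that no such method is named and no route from the fallback to the success rule is stated.
- A reader might infer a definite loss of precision. No figure can be given: the protocol states no baseline-outcome correlation and does not say that the fallback would ignore baseline. The 620 also reproduces from an unadjusted formula, so the planned power did not rely on adjustment.

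It is also fair to say that change is an imperfect proxy and not an unrelated quantity. With baseline as a covariate, modelling change or the follow-up score gives the same treatment effect and residuals. That supports checking those residuals; it does not support checking the marginal change.

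The reply does not remove the point. The check on change, the permitted fallback and the points-based criterion are all stated in the same section, so this is not detail left to the SAP.

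**Conclusion.** The point holds in a limited form. The protocol checks an imperfect proxy for the model's assumption. It also permits, for the primary outcome, an analysis that may not yield the LLFDI-point difference on which success is defined.

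At about 279 evaluable patients per arm there is little to gain from such a switch. Under the assumed skewness, the untransformed adjusted difference kept type I error near 5% and coverage near 95%, even when normality was rejected in every run. When only the baseline was skewed, change looked non-normal in 53–55% of runs although the model was correct.

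These sizes are illustrative. They rest on one follow-up visit, an assumed correlation of 0.5, assumed distributions and an assumed test, and the planned repeated-measures model was not itself simulated. The protocol does not suggest that LLFDI scores have these shapes. The inconsistency between the fallback and the success rule does not depend on the simulations. It should be corrected, but the sample size is not in question.

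**What to change.** Amend the Statistical analysis section, and the SAP to match:

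1. State that the mixed-model adjusted mean difference on the LLFDI scale is the primary analysis whatever the distributional assessment shows, and that the success rule is read from its confidence interval.
2. Replace the formal assessment of change from baseline with graphical inspection of the model residuals.
3. Pre-specify robust (sandwich) or bootstrap confidence intervals for the same mean difference as a sensitivity analysis. Keep any transformed or rank analysis as a sensitivity analysis only.
4. Apply the same approach to the continuous secondary outcomes.

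The cost is wording and one sensitivity analysis. The sample size and data collection do not change.

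### The success rule requires the lower 95% confidence limit to exceed the same 3 points the trial is powered to detect, so at the planned effect it is met 2.5% of the time

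*Protocol article*

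**What the plan says.** Two sections of the protocol article bear on this.

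- **Sample size.** The calculation starts from a standardised effect: "our sample size calculation is based on a moderately small standardised effect size of 0.275". The authors expect an effect of this size to be clinically important. The 620 participants (310 per arm, allowing 10% loss to follow-up) are "required to detect a standardised effect size of 0.275 with 90 % power", at "5 % (two-sided) significance". In scale units: "This standardised effect size is equivalent to detecting around a 3-point difference on the LLFDI between treatment arms assuming a standard deviation of 10.91".
- **Statistical analysis.** The decision rule reads "The trial will be deemed a success based on the primary outcome of the total LLFDI", and it names two conditions joined by 'and': the p value, and that the lower bound of the 95% "CI is greater than 3 points".

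No part of the article assumes a true effect above 3 points or sizes the trial for the second condition.

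**The concern.** The same 3 points serve two incompatible purposes. In the sample size they are the true difference the trial should be able to distinguish from zero. In the success rule they are the margin the whole confidence interval must clear. Clearing a margin of 3 is a different and much harder hypothesis than excluding zero, and the stated 90% power belongs only to the latter.

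At stake is the headline conclusion on the primary outcome. A programme that truly delivers the benefit the protocol regards as worthwhile would miss the success criterion about 97.5% of the time. An observed difference of 3 or 4 points would be significant against zero, as the sample size intends, and would still not count as success.

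**Working it through.** **Inputs.** All from Sample size: standardised effect 0.275, standard deviation 10.91, power 90%, two-sided 5%, 10% loss, 310 per arm. From Statistical analysis: margin of 3 points for the lower 95% limit. The planned effect in points is 0.275 × 10.91 = 3.00025, so the word 'around' hides no meaningful gap between effect and margin.

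**1. Reproduce the stated sample size.**

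n per arm = 2 × (1.960 + 1.282)² / 0.275² = 277.9, so 278 by the normal approximation. The noncentral t calculation gives 279. Inflating for loss: 279 / 0.9 = 310 per arm, total 620. The stated figure reproduces, and it does so as a test against zero. Power against zero at 279 per arm and a true difference of 3 is 90.1%.

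**2. Probability of meeting the success rule.**

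SE = 10.91 × √(2/279) = 0.924.

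The lower limit exceeds 3 when the observed difference exceeds 3 + 1.96 × 0.924 = 4.81 points (0.44 SD). For comparison, significance against zero needs only 1.96 × 0.924 = 1.81 points.

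For a true difference d, P(success) = Φ((d − 3)/SE − 1.96).

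| True difference (points) | 279 per arm (10% loss) | 310 per arm (no loss) |
|---|---|---|
| 3 | 2.5% | 2.5% |
| 4 | 19.0% | 20.6% |
| 5 | 58.1% | 62.6% |
| 6 | 90.1% | 92.8% |

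At d = 3 the first term vanishes and the result is Φ(−1.96) = 2.5%, whatever the standard error.

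**3. True difference needed for a given chance of success (279 per arm).**

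- 90%: 3 + (1.960 + 1.282) × 0.924 = 5.99 points, a standardised effect of 0.55.
- 80%: 3 + (1.960 + 0.842) × 0.924 = 5.59 points.

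**4. Does the planned model rescue the rule?**

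The analysis adjusts for baseline, which shrinks the standard error by √(1 − ρ²). The article gives no ρ, so these are assumptions:

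| Assumed ρ | SE | P(success) at 3 points | True difference for 90% |
|---|---|---|---|
| 0.3 | 0.881 | 2.5% | 5.86 |
| 0.5 | 0.800 | 2.5% | 5.59 |
| 0.7 | 0.660 | 2.5% | 5.14 |

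**5. The p-value condition.** A lower limit above 3 already lies above zero, so two-sided p < 0.05 follows. The clause adds nothing to the rule as written.

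**The case against.** Several points can fairly be made for the plan.

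- *A strict margin is legitimate.* It is, but then the trial needs a power statement for that margin and a reason to expect an effect well above 3 points. The Sample size section gives neither, and it says there is little information on the likely treatment difference.
- *The 90% was never claimed for the success rule.* Correct: it is claimed for detecting 0.275. The precise criticism is that the declared rule has no matching power statement and, at the planned effect, very little chance of being met.
- *The trial still answers its question.* This stands in part. The article commits to a difference in means with a 95% confidence interval, and that comparison keeps 90% power against zero. The defect is in the success criterion, not in the data or the estimate. The article also does not say how a result that misses the criterion would be reported.
- *The 2.5% depends on the standard deviation being 10.91.* This stands as a qualification. The figure holds when the true difference is 3 points. If the effect is instead fixed at 0.275 SD and the SD differs, the true difference in points moves. With 279 per arm and assumed SDs of 8, 15 and 20, the true differences are 2.2, 4.125 and 5.5 points and the chance of success is about 0.1%, 14% and 31%. The direction does not change. The monitoring committee is to review the SD, but that does not alter the rule.
- *It may be a drafting slip.* Because the p-value clause is redundant, the authors may have meant a point estimate of at least 3, or a lower limit above 0. In that case the sentence is still wrong as printed and governs the primary outcome.

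**Conclusion.** The concern holds. The sample size and the success rule test different hypotheses, and the margin in the rule equals the planned effect. At a true difference of 3 points the rule is met 2.5% of the time, independent of sample size, loss to follow-up and covariate adjustment. With 279 analysed per arm, SD 10.91 and no baseline adjustment, 90% needs a true difference of about 6 points; with an assumed baseline correlation of 0.3 to 0.7 it needs about 5.9 to 5.1 points. The calculation uses a normal approximation and takes a positive difference to favour the intervention, as the rule implies. This must be corrected before the final comparison is made.

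**What to change.** Replace the success sentence in Statistical analysis with wording such as: 'Effectiveness is concluded if the 12-month difference in total LLFDI favours the intervention with two-sided p < 0.05 (95% confidence interval excluding 0). The estimate and its interval are then interpreted against the 3-point difference.' This matches the 620 participants already justified.

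If the sponsor intends the 3-point margin, keep it and add the power that belongs to it: 2.5% at a true difference of 3 points and 90% only at about 6 points unadjusted, or the corresponding figure under a stated baseline correlation.

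The change is one sentence in the protocol, carried into the SAP, with no extra patients or data. Because it relaxes a success criterion during recruitment (210 recruited by the end of August 2016) and the monitoring committee may see data by arm, it should be a dated, justified amendment, made before data lock by people blind to comparative results. The article plans no formal interim analysis of effectiveness and has the SAP approved before data lock and before allocation is added to the database, so this is feasible.
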